## Abstract

**Introduction:**

Delayed neurocognitive recovery, also identified as early postoperative cognitive decline (POCD), is a common complication after surgery, with advanced age being the most important risk factor. As the geriatric population is increasing worldwide, and number of older adults undergoing surgery continues to rise, so will the incidence of POCD. Only a small proportion use digital cognitive tests for measuring postoperative neurocognitive performance compared with analogue tests. This study aims to evaluate a digital cognitive screening tool, Mindmore Postoperative version (Mindmore-P), in a perioperative setting to determine its feasibility and usability, and to compare preoperative cognition with early postoperative neurocognitive performance. Further, to determine associations between neurocognitive performance and perioperative factors as well as to explore patients’ experiences of early neurocognitive recovery.

**Methods and analysis:**

We will include 50 patients (aged ≥60 years) undergoing elective abdominal surgery under general anaesthesia. Cognitive functions will be measured with Mindmore-P preoperatively and on postoperative day (POD) 1 or 2 as well as 2–3 weeks after surgery. Preoperatively, frailty, (Clinical Frailty Scale), depression (Geriatric Depression Scale-15), functional status (12-item WHO Disability Assessment Schedule 2.0) and pre-recovery status (Swedish web version Quality of Recovery Scale, SwQoR) will be measured. Delirium will be assessed by Nu-DESC (Nursing Delirium Screening Scale) twice a day, with start on POD 1 and until the patient is discharged from the hospital. Outcomes at 2–3 weeks postoperatively are postoperative recovery (SwQoR), depression, functional status and usability (System Usability Scale) of Mindmore-P. Postoperative recovery will also be measured POD 1 or 2. We will also explore feasibility and experience of early postoperative neurocognitive recovery with interviews approximately 1 month after surgery.

**Ethics and dissemination:**

This study is approved by the Swedish Ethical Review Authority (REC Reference: 2022-03593-01) and will follow the principles outlined in the 1964 Helsinki Declaration and its later amendments. Results from this study will be disseminated in peer-reviewed journals, scientific conferences and in social media.

**Trial registration number:**

NCT05564195.

STRENGTHS AND LIMITATIONS OF THIS STUDYThis study follows the Medical Research Council’s framework for designing and evaluating complex interventions.This study will provide evidence for the feasibility and usability of a digital neurocognitive tool to be used in a population of older persons undergoing surgery.This pilot study will create a knowledge base for future interventions as previous studies are lacking.A limitation is that the study only includes two follow-ups.

## Introduction

The geriatric population is increasing worldwide.^1^ Every fifth person in Sweden today is ≥65 years, and the number of persons of 80 years and over is estimated to increase by 50% until 2050.^2 3^ National statistics show that approximately 700 000 people undergo inpatient surgery, and almost 50% of those are performed on people ≥60 years.^4^ However, hospital care after surgery remains short for the afflicted population; hence a major part of the postoperative recovery occurs after discharge from the hospital which^2^ poses several risks for older people such as cognitive decline.^1^

Cognitive decline in older individuals has become an area of great concern, particularly given the impact of cognitive impairment on functional capacity.^5^ Cognitive functions in late adulthood decline at different pace, and some cognitive domains are more prone to faster decline, such as executive functions, speed processing and memory.^6^ Delayed neurocognitive recovery, earlier identified as postoperative cognitive decline (POCD), is an early postoperative cognitive complication, included in perioperative neurocognitive disorders. Delayed neurocognitive recovery is diagnosed up to 30 days after anaesthesia and surgery^1 7^ and is characterised by a gradual decreased performance in several cognitive domains such as memory, speed processing, executive function and attention.^1 8^ The term POCD will be used in this article when referring to earlier research.

The methods used for measuring postoperative neurocognitive performance vary widely between studies, with only a small proportion, 13.5%, using digital cognitive tests or a combination of analogue and digital tests.^15^ To cover this gap we conducted a comparability study^16^ between the digital cognitive test battery Mindmore Postoperative version (Mindmore-P), and the analogue International Study Group of Postoperative Cognitive Dysfunction (ISPOCD) test battery.^17^ The study included 50 cognitively healthy participants aged 60 years and older. We found that the included tests in ISPOCD and Mindmore-P were comparable. Further, the participants were overall positive to digital testing and thought that neurocognitive testing was useful and important to assess if they would undergo surgery (Manuscript in progress). The next step, following Medical Research Council’s framework for designing and evaluating complex interventions,^18^ is to assess predefined progression criteria to reduce uncertainty around recruitment, data collection, outcomes, sample size and analysis in a future intervention study.

### Aim

The aim of this study is to pilot test Mindmore-P in a clinical perioperative setting. To achieve this, we intend:

To test the recruitment process and measure attrition rate.To determine the usability and feasibility of Mindmore-P.To explore the trajectory of delayed neurocognitive recovery by measuring the patient’s preoperative and postoperative neurocognitive performance.To investigate if there are any associations between the dependent variable; delayed neurocognitive recovery and the independent variables; delirium, preoperative frailty, symptoms of depression, postoperative delirium, physical function, and early postoperative recovery.To determine patients’ experiences of early neurocognitive recovery.

## Methods and analysis

### Study design

This is an observational feasibility study.

### Participants, recruitment, and setting

We will include 50 patients undergoing elective abdominal surgery under general anaesthesia at Ersta Hospital in Stockholm, Sweden. Patient recruitment is planned to start in December 2022 and end in July 2024. The sample size is guided by a reported incidence of early cognitive decline of approximately 13%–25% at 1–2 weeks postoperatively. 17 At the patient’s preoperative outpatient visit, a research nurse will provide oral and written information about the study. The details of the study and its potential benefits and risks will be explained carefully to the patient. If the patients agree to participate in the study, they will undergo a Mini-Mental State Examination (MMSE) screening with the research nurse to examine if they are eligible for the study.

#### Inclusion criteria

≥60 years of age undergoing elective non-cardiac surgery with general anaesthesia.Duration of surgery >60 minMMSE score >24.

#### Exclusion criteria

MMSE score <23 indicating cognitive impairment.^19^Inability to read and speak Swedish.Uncorrected severe visual or auditory disorder, disease of the central nervous system, psychiatric diseases including alcohol abuse or drug dependence, current motor impairment in dominant hand, and colour vision deficiency.

### Outcomes

#### Cognitive tests

The intervention is the digital cognitive test battery Mindmore-P (table 1), which will assess neurocognitive performance. The test battery measures the following cognitive domains: verbal episodic memory, executive functions, visuospatial function and attention.

**Table 1 T1:** Included tests and cognitive domains in the Mindmore-P

Cognitive domain	Mindmore-P
Verbal episodic memory	Consortium to Establish a Registry for Alzheimer’s Disease (CERAD) A 10-word verbal learning test with three learning trials, a recall trial after ~7 min. Words are read and visually presented on the screen and the patient replies in speech.
Executive function, visuospatial function	Trail Making Test (TMT-A and B) Each part consists of 25 circles with letters or numbers on the screen. In part A, the circles are numbered from 1 to 25. The patient is instructed to draw a line between them in ascending order of numbers, from 1 to 25, as rapidly as possible. Part B consists of 13 digits and 12 letters to be paired, and the test subject is instructed to draw a line between them in ascending number and letter order.
Executive function, selective attention	Stroop Colour-Word Test (SCW) 24 words spelling out the name of a colour which is printed in contrasting ink colours (eg, the word ‘green’ printed with red ink), and the participant is asked to tell the printed colour of the word rather than the actual meaning of the word.
Executive function, visuospatial function	Symbol Digits Processing Test (SDPT) The test consists of nine symbol–digit pairings at the top of the screen, one symbol in the middle of the screen and a 3*×*3 number grid at the bottom of the screen. The participant is required to associate the symbol in the middle to one of the digits on the grid below. As soon as a choice is made a new symbol appears. The final score is the number of correct matches in 90 s

Mindmore-P, Mindmore Postoperative version.

The Mindmore-P is self-administered on a touch screen tablet (10.1″ 20–30 min Windows), and is a web application running on a full-screen Chrome browser. The test is administered by using a capacitive touchscreen with features that record detailed information such as timing, pauses and lifting of finger from the touchscreen. Speech recognition is used in the screening of verbal memory and language. Mindmore’s platform is CE certified and includes normative data adjusted for age, education and sex^20^

#### Usability

The usability (table 2) of Mindmore-P will be assessed with the System Usability Scale (SUS). SUS consists of 10 items to be answered on a 5-point scale from ‘strongly agree’ to ‘strongly disagree’.^21^

**Table 2 T2:** Outcome measures

Outcome measures	Questionnaires	Preop	POD 1 or POD 2	Revisit at hospital POD 14+0–5 days	One month postop
Dependent variable					
Postoperative neurocognitive recovery	Mindmore-P	X	X	X	
Independent variables					
Frailty	Clinical Frailty Scale	X			
Depression	GDS-15	X		X	
Functional capacity	WHODAS-12	X		X	
Daily delirium assessment with start on day of surgery	Nu-DESC				
Postoperative recovery	SwQoR	X	X	X	
Usability of Mindmore-P	SUS			X	
Feasibility: experiences of neurocognitive recovery and digital assessment	Qualitative interviews				X

GDS-15, Geriatric Depression Scale-15; Mindmore-P, Mindmore Postoperative version; POD, postoperative day; SUS, System Usability Scale; SwQoR, Swedish web version of Quality of Recovery; WHODAS-12, 12-item WHO Disability Assessment Schedule 2.0.

#### Depression screening

The Geriatric Depression Scale (GDS) is a widely used instrument to screen for depression in the older adult population.^22^ The GDS-15 consists of 15 items with binary answer (yes/no) to questions such as ‘*Do you feel helpless*?’ or ‘*Are you in good spirits most of the time*?’.^23^ The cut-off score is standardised with a score of 6 to the Swedish older adult population.^24^ Every participant will answer the Swedish version of the GDS-15 before surgery and on postoperative day (POD) 14 during the revisit at the hospital.

#### Preoperative frailty

Preoperative frailty will be measured by using the 9-item Clinical Frailty Scale (CFS), translated to a Swedish version, the scale ranges from 1 *very vital* to 9 *terminally ill*. The Swedish version has been validated in persons >65 years seeking care at an emergency department.^25^

#### Delirium assessment

Delirium assessment will be performed using the observational 5-item scale Nu-DESC, where symptoms are rated from 0 to 2. A score of 2 or more indicates delirium.^26^ A Swedish version of the Nu-DESC has been validated in persons undergoing cardiac surgery.^27^

#### Postoperative recovery

Postoperative recovery will be measured with Swedish web version of Quality of Recovery (SwQoR). SwQoR is a psychometric evaluated including 24 different symptoms such as fatigue, nausea, anxiety, headache, pain in the surgical wound, fever, to be rated on 11-point numerical scales from 0 ‘never’ to 10 ‘always’.^28^ Global score ranging from 0 ‘excellent quality of postoperative recovery/no symptoms’ to 240 ‘extremely poor quality of recovery/severe symptoms’, with cut-off values less than 31 at POD 7 and less than 21 on POD 14 indicating good recovery.^29^ Reliability and validity tests have presented evidence that it is suitable to use SwQoR in patients undergoing surgery.^28^

#### Functional capacity

Functional status (table 2) will be measured with the Swedish version of 12-item WHO Disability Assessment Schedule 2.0 (WHODAS), ranges from 0 to 48, with increasing scores reflecting increasing disability.^30^

#### Demographic and perioperative data

These include age, sex, educational level, MMSE score, comorbidities, American Society of Anaesthesiologists classification, premedication, choice of anaesthetic drugs, duration of anaesthesia and surgery, type of anaesthesia and surgery, intraoperative bleeding (mL), postoperative pain scores (numeric rating scale), intraoperative and postoperative opioids, early postoperative complications, and length of hospital stay.

#### Feasibility and patients’ experiences of early postoperative cognitive recovery

Approximately 20–25 of the study participants will be included in an individual face-to-face interview exploring patients’ experiences of early neurocognitive recovery and the use of Mindmore-P. The sample size will follow the concept of information power and will be determined within the process of data collection. Information power means that the more information the sample has, the lower the need to increase the amount of participants.^31^ A semistructured interview guide will be constructed and tested; examples on questions from the interview guide are ‘*Can you tell me about how you have been since you were discharged from the hospital?’* To gain a deeper understanding, probing questions will be asked, such as: ‘*Have you experienced any changes in your memory since the surgery?’, ‘how has it been to plan and do different tasks after the surgery?’* and ‘*you mentioned …’, ‘Could you tell me more about that?’, ‘how do you mean* and *how would you describe that*?’ and ‘*Can you give me any example?’*. The participants will be asked to speak freely about their experiences of their postoperative neurocognitive recovery. All interviews will be audiotaped.

### Procedure

#### Preoperative data collection

Eligible patients who consent to participate in the study will undergo the cognitive Mindmore-P test battery preoperatively. Before the test battery starts, we will inform about the Mindmore-P procedure and during the first test session a trained research nurse will be present in the room to assist with any technical help needed. Each test consists of an introduction both in audio and visualised on-screen, and the instructions can be repeated on demand. A practice trial is performed before the test battery starts. The digital cognitive test is expected to take less than 30 min. Depression, frailty, postoperative recovery (except for three questions about the surgical wound) and functional status will be measured after the cognitive testing is completed by the trained research nurses (table 2). It is estimated to take 15–20 min to complete the questionnaires. The day and time of day for preoperative data collection will be documented.

#### Postoperative data collection

We will assess delirium (Nu-DESC) twice a day (morning and afternoon) with start on POD 1 and until the patient is discharged from the hospital. Postoperative neurocognitive performance (Mindmore-P) and postoperative recovery (SwQoR) will be measured on POD 1 or 2, and at the follow-up visit approximately 2 weeks after the surgery. We will measure depression (GDS-15), functional status (WHODAS) and usability of Mindmore-P (SUS) at the follow-up visit. Feasibility and experience of postoperative neurocognitive recovery will be assessed with interviews approximately 1 month after surgery in the patient’s home or at the hospital (table 2).

### Analysis

Descriptive statistics of demographic data will be presented with number, percentage and mean (SD) or range, as appropriate. A within-subject analysis and a standardised reliable change Z-score for each postoperative neurocognitive test (n=4) will be calculated, based on the difference between patient’s test results at baseline (i.e., preoperative) versus postoperative tests results, and normalised using Mindmore’s normative data for each specific test.^20^ As recommended by Borchers *et al* review from 2021, mild POCD (1–2 SD) and major POCD (>2 SD) will be specified for each test result and POCD is present if at least two tests indicate decline.^15^

Usability and attrition rates will be presented with descriptive statistics. Demographic characteristics, potential cofounders (i.e., patients characteristics, surgical and anaesthesiologic factors), preoperative depression (GDS-15), frailty (CFS), postoperative recovery (SwQoR) and functional status (WHODAS) will be compared between the groups, that is, delayed neurocognitive recovery or not, using parametric and non-parametric tests. To analyse intraindividual differences over time in cognitive performance, the same statistical tests as well as multivariate logistic regression analysis will be used. A p-value of <0.05 will indicate statistical significance in all analyses. We will analyse the interviews with thematic analysis.^32^

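### Unless the Mindmore norms hold retest data, the planned reliable change Z-score neither removes practice gain nor scales by the SD of change, and the delayed-recovery label is likely biased

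*Protocol article*

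**What the plan says.** The Analysis section of the protocol article states that "a standardised reliable change Z-score for each postoperative neurocognitive test (n=4) will be calculated". The score starts from the difference between the preoperative result and the postoperative results, "versus postoperative tests results, and normalised using Mindmore’s normative data for each specific test". The section on cognitive tests says of the platform only that it "includes normative data adjusted for age, education and sex".

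Severity thresholds are then applied to the single tests: "mild POCD (1–2 SD) and major POCD (>2 SD) will be specified for each test result". The rule for the patient as a whole counts how many tests are affected: "POCD is present if at least two tests indicate decline". The battery is given three times: "Cognitive functions will be measured with Mindmore-P preoperatively and on postoperative day (POD) 1 or 2 as well as 2–3 weeks after surgery". Table 2 lists "Postoperative neurocognitive recovery", measured with Mindmore-P, as the dependent variable. The Analysis section compares patients with and without delayed neurocognitive recovery on depression, frailty, recovery, function and potential confounders. The Discussion says that the pilot will guide the choice of primary outcome and the sample size of a future study.

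The article writes out no formula for the Z-score. It gives no retest correlation, expected retest change or SD of change, and describes no non-operated group tested twice.

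**The concern.** A reliable change index needs two quantities: the change expected on retesting without any insult, which is subtracted, and the SD of that change, which is the divisor. Norms adjusted for age, education and sex give the expected score and spread at one session. That is a different thing.

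Word learning, trail making, Stroop and symbol-digit tasks can plausibly improve on repetition. If that gain is left in, it offsets true decline. If the divisor is the between-person SD, a decline of 1 SD carries a different chance rate for each test, depending on that test's retest correlation.

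At stake are the reported incidence of delayed recovery, the two groups formed for the association aim, and whatever incidence is carried into the sample size of the future study.

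**Working it through.** **Nothing to reproduce.** The documents give no figure for reliability, practice gain or misclassification. The values of r, g and ρ below are assumptions.

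**Step 1: what the norms contribute.** Let μ and σ be the norm mean and SD for a patient's age, education and sex. These are effectively the same at each session, so

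(post − μ)/σ − (pre − μ)/σ = (post − pre)/σ.

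The mean cancels and only a single-session SD remains.

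**Step 2: distribution of change.** Let r be the retest correlation and g the practice gain in normative SDs. Assume equal SDs at both sessions, normal changes, and scores oriented so that higher is better. With no true change, the change in normative SD units is N(g, 2(1 − r)). The SD of change is √(2(1 − r)):

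- r = 0.5: √1.0 = 1.00
- r = 0.7: √0.6 = 0.77
- r = 0.8: √0.4 = 0.63

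**Step 3: one test, no true change, no gain.** P(decline of at least 1 SD) = Φ(−1/√(2(1 − r))) = 15.9%, 9.8% and 5.7% for r = 0.5, 0.7 and 0.8. The same label covers nearly a threefold range.

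**Step 4: the two-of-four rule.** Assume the same r and g for all four tests and a correlation of ρ = 0.3 between the tests' changes. The comparator is Z = (change − g)/√(2(1 − r)), cut at −1.

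| r | g | Norm-scaled: no true change flagged | Norm-scaled: true 1 SD loss on all four tests detected | Retest-based: no true change flagged | Retest-based: true loss detected |
|---|---|---|---|---|---|
| 0.5 | 0 | 15.6% | 63% | 15.6% | 63% |
| 0.5 | 0.3 | 7.9% | 47% | 15.6% | 63% |
| 0.5 | 0.5 | 4.7% | 37% | 15.6% | 63% |
| 0.7 | 0 | 8.1% | 63% | 15.6% | 77% |
| 0.7 | 0.3 | 2.8% | 42% | 15.6% | 77% |
| 0.7 | 0.5 | 1.2% | 30% | 15.6% | 77% |

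**Step 5: direction.** The norm-scaled cut of −1 equals a cut of −(1 + g)/√(2(1 − r)) on the retest-based scale. At r = 0.7 this is −1/0.775 = −1.29, −1.3/0.775 = −1.68 and −1.5/0.775 = −1.94 for g = 0, 0.3 and 0.5. The norm-scaled rule is stricter whenever 1 + g exceeds √(2(1 − r)). With no gain, that means r above 0.5. Below 0.5 with no gain it over-flags: at r = 0.4, one unchanged test is flagged with probability Φ(−1/1.095) = 18.1%.

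The lower detection therefore comes with fewer false positives. What is lost is the stated meaning of 1 SD, and with it the meaning of the incidence.

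**Step 6: chance rate in this study.** With 50 patients and no true change in any of them, the retest-based rule flags 50 × 0.156 = 7.8 on average. The incidence of 13%–25% cited under Participants corresponds to 6.5–12.5 patients.

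**The case against.** A reader might infer that the norms certainly lack retest data and that patients will certainly be misclassified. The documents do not support that. The norms come from a cited source that is not at hand, the description in the cognitive-tests section is brief, and the divisor is never written out. The source may hold retest data. The size and direction of any error also depend on r and g, which the documents do not give. At r = 0.5 with no gain the two indices are identical, and below 0.5 the scaling error reverses.

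Nor can one say that the three administrations fall within about three weeks. Table 2 fixes the last one at postoperative day 14 plus 0–5 days, but the interval from the preoperative visit to surgery is not stated. The Procedure section provides a practice trial, repeatable instructions and a nurse present at the first session. These may reduce practice gain, but they neither measure nor remove it.

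It is also fair to say that this is an observational feasibility study that opens with recruitment, attrition and usability aims. It plans a separate within-subject analysis of change over time, and its test scores can be rescored later.

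What stands is the stated rule. The article names the numerator and the normaliser, and calls the result reliable change. As described, that normaliser cannot supply reliable change, and nothing else in the design does. This is more than a formula that a condensed article leaves to a fuller document.

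**Conclusion.** The concern holds conditionally. If the norms are single-session, as the article's description reads, the Z-score is change in normative SD units and not reliable change. The delayed-recovery label is then likely biased, mainly towards under-detection when r exceeds 0.5 or practice gain is present. Under the assumptions r = 0.7 and ρ = 0.3, detection of a true 1 SD loss on all four tests is 63%, 42% and 30% at gains of 0, 0.3 and 0.5 SD, against 77% for a retest-based index. If the norms do include retest data and the plan uses them, the problem disappears.

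This should be fixed, but it does not undermine the feasibility aims. It matters most for the association analysis and for any incidence passed on to the next study.

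**What to change.** State the formula and whether the norms include retest data.

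- **If retest data exist** from non-operated people aged 60 or over, define for each test Z = (patient's change − mean retest change) / SD of retest change. The normative sample is one possible source. The 50 healthy participants of the comparability study are another, but only if they were tested twice, which the article does not say. Use retest intervals as close as possible to those in the study.
- **If none exist**, call the index change in normative SD units. Do not present it as reliable change, or as an incidence of POCD to be carried into the future sample size. Report the classification over a stated grid, for example r from 0.5 to 0.8 and practice gain from 0 to 0.5 SD.

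The cost is wording and analysis time, with no new patients or visits. There is one real downside. With the retest-based index, the 1 SD, two-of-four rule flags about 16% of patients with no true change (ρ = 0.3), whatever the retest correlation. At r = 0.7 the norm-scaled score flags about 8% with no gain and 3% with a gain of 0.3 SD. The 16% lies inside the cited incidence of 13%–25%, so the chance rate should be reported beside the observed incidence.
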